All groups 1, 2, 5, and 6 receive the full combined intervention (hypnosis + essential oil) in Phase 1, ensuring that Groups 5 and 6 have the same conditioning opportunity as their counterparts before the switch. Groups 3 and 4 allow us to isolate the effects of hypnosis itself (Group 3) and to account for any changes over time not attributable to the interventions (Group 4). Randomization is implemented via the SoSci Survey platform's built-in algorithm once participants are deemed eligible, ensuring allocation concealment. Because of the nature of the interventions, participants will know if they are using an oil or not (blinding is not feasible on the user level), but they will not be informed of the study hypotheses regarding which combination is expected to be most effective. The trial is single blinded in that the data analysts/statisticians will remain blind to group labels until after the primary analyses are completed, to prevent bias in outcome analysis.

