**Exploratory Hypothesis 2.3 (Moderators of Effect).** We will explore whether certain baseline factors moderate the intervention's effectiveness. Demographic factors like age, gender, or socioeconomic status might influence outcomes. For instance, it's possible that participants with higher initial anxiety, though still subthreshold, benefit more or less from the intervention, or that younger vs. older participants have different adherence rates. These analyses are exploratory and will be used to generate hypotheses for which subgroups respond best to this approach.

**Exploratory Hypothesis 2.4 (Physiological Effects).** We hypothesize that the combination of hypnosis and aromatherapy yields measurable physiological relaxation, reflected in increased parasympathetic activity or reduced sympathetic activity compared to hypnosis alone. In the laboratory subgroup, it is hypothesized that Group 1/2 (combined) will demonstrate larger increases in HRV, particularly high-frequency HRV, which is indicative of parasympathetic tone, and/or a greater reduction in heart rate and PWV from T0 to T1 than Group 3 (hypnosis only). This would suggest an additive effect of the essential oil on the body's relaxation response, consistent with objective evidence that an essential oil can modulate autonomic activity. However, given sample size limitations, this will be an exploratory outcome.

**Exploratory Hypothesis 2.5 (VAS Trajectory and Learning Effects).** By examining the VAS relaxation ratings collected before and after each session, we hypothesize that participants receiving the combined intervention will not only have larger acute relaxation gains per session on average than those in comparison groups, but they may also exhibit learning effects over time. A learning effect would manifest as gradually higher pre-session relaxation levels as weeks progress the participant's baseline state before each session improves, indicating they carry over some relaxed state or become more skilled at self-relaxation. We expect such effects might be most pronounced in those who undergo conditioning (Groups 1 and 2), potentially showing an upward drift in pre-session VAS scores and/or a plateau indicating habituation to relaxation. We will explore and graph these trajectories for insight into how the relaxation response develops with practice.

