### Data analysis

2.13

The primary outcome (MDBF calmness subscale change from T0 to T1) will be analyzed using an ANCOVA model. The model will include the study group (4 arms for primary analysis: Groups 1–4) as the independent variable and the baseline MDBF score as a covariate to control for any initial differences and improve statistical power. This aligns with the principle of analyzing covariance to account for baseline variance. The primary contrast of interest is whether either of the two combination groups (1: Hypnosis + Bergamot, 2: Hypnosis + Lavender) differ significantly from the control groups (3: Hypnosis-only, 4: Minimal intervention) in adjusted mean relaxation at T1. We anticipate a significant overall group effect; planned pairwise comparisons with appropriate correction for multiple comparisons, if needed, will examine specific differences, especially 1 vs. 3, 2 vs. 3, and combined 1&2 vs. combined 3&4. The primary hypothesis will be supported if Groups 1 and 2 show statistically greater increases in relaxation than Group 3 and Group 4 (*p* < .05, two-tailed).

For Phase 2 conditioning effects, a similar ANCOVA or mixed-model approach will be used at T2. The analysis will focus on the four groups that underwent Phase 2 aroma testing (Groups 1, 2 with match vs. Groups 5, 6 with mismatch). We will compare relaxation outcomes at T2 among these, using T1 values as covariates. A significant difference (e.g., match > mismatch) on the MDBF relaxation change from T1 to T2 or on the Phase 2 VAS responses would support H2.1. We may also use repeated measurements ANOVA or multilevel modeling incorporating all three time points (T0, T1, T2) to examine group × time interactions across the full study duration. The VAS data from each session will be analyzed using linear mixed-effects models, which can handle multiple observations per participant. These models will test differences in immediate relaxation gain per session by group and can also model time trends (session number as a predictor) to see if there is a significant upward trend in pre-session relaxation over the 6 weeks for each group (learning effect).

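### Exploratory H2.5: the learning effect is sought as an upward pre-session VAS trend within each group, with no between-group slope comparison, so a drift shared by all arms could be read as learning

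*Protocol article*

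**What the plan says.** Section 2.10 of the Protocol article introduces the analysis under the heading "Exploratory Hypothesis 2.5 (VAS Trajectory and Learning Effects"). It expects participants on the combined intervention to have "larger acute relaxation gains per session on average than those in comparison groups, but they may also exhibit learning effects over time". It then says what learning would look like: "A learning effect would manifest as gradually higher pre-session relaxation levels as weeks progress". The expectation about the arms follows: "We expect such effects might be most pronounced in those who undergo conditioning (Groups 1 and 2").

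Section 2.13 gives the session-level VAS data two analyses within the same mixed models. The first compares arms: "These models will test differences in immediate relaxation gain per session by group". The second enters session number in the model, with this aim: "to see if there is a significant upward trend in pre-session relaxation over the 6 weeks for each group (learning effect"). The only group × time interaction named in 2.13 is an optional model "incorporating all three time points (T0, T1, T2) to examine group × time interactions across the full study duration". It concerns the three main assessments, not the session ratings.

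Section 2.6 says that one purpose of the comparison arms is "to account for any changes over time not attributable to the interventions (Group 4").

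**The concern.** The null hypothesis of the stated trend analysis is that pre-session relaxation does not change with session number in a given arm. The null hypothesis that matters for a claim about the combined intervention is that its slope equals that of a comparison arm. The two differ whenever ratings drift for reasons shared by all arms, such as repeated self-rating or growing familiarity with the scale. A test against zero picks up that drift together with any learning and cannot separate them.

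Two readings of the results would then be open to error. A significant upward slope in Groups 1 and 2 could be reported as learning when every arm rose equally. And a significant slope in Group 1 or 2 beside a non-significant one in Group 3 could be taken as learning added by the oil, although a difference in significance is not a test of a difference. The trial has randomised comparators that would settle the matter, but the text does not say that they will be used for it.

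**Working it through.** The plan states no figure for this analysis, so there is none to reproduce. The check asks how often the stated test is significant when all arms share one drift and the intervention adds nothing.

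**From the protocol:** a 0–100 VAS and a session every two days for six weeks (2.7), hence about 21 sessions; 105 participants per arm and dropout of up to about 35% (2.11), hence about 105 × 0.65 = 68 completers in the worst case.

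**Assumed, because the protocol gives no value:** two-sided α of 0.05 for the trend; within-person SD σ; between-person SD τ of the six-week slope; common drift D; all 21 ratings completed.

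**Variance of one participant's slope.** Put time on a 0–1 scale with 21 equally spaced sessions. The sum of squared centred times is Sxx = 770/400 = 1.925, and V = τ² + σ²/Sxx.

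**Standard error of one arm's mean slope:** SE = √(V/n).

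**Chance of a significant upward trend in one arm:** approximately Φ(D/SE − 1.96).

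For n = 105 and D = 3:

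| σ / τ | V | SE | D/SE − 1.96 | Chance |
|---|---|---|---|---|
| 12 / 5 | 25 + 74.8 = 99.8 | 0.975 | 1.12 | 87% |
| 15 / 10 | 100 + 116.9 = 216.9 | 1.437 | 0.13 | 55% |
| 15 / 15 | 225 + 116.9 = 341.9 | 1.804 | −0.30 | 38% |
| 20 / 15 | 225 + 207.8 = 432.8 | 2.030 | −0.48 | 31% |

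Simulation gave 86.5%, 55.2% and 29.8% for the first, second and fourth rows. A still larger slope SD (σ/τ = 18/20) gives 25%. At D = 5 the 15/10 and 15/15 rows become about 93% and 79%. At n = 68 and D = 3 they are about 38% and 27%. At D = 0 the chance is the nominal 2.5%.

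**Split significance.** With one-arm probability p, the chance that Group 1 or 2 is significant while Group 3 is not is [1 − (1 − p)²](1 − p). For 15/15 and D = 3, p = 0.383, which gives 0.619 × 0.617 = 0.38; simulation gave 0.387. At D = 5 it is about 0.20. None of these trials contains a difference between arms.

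**Between-arm contrast.** For Groups 1 and 2 together (210) against Group 3 (105), the standard error is √[V(1/210 + 1/105)] = √1.5 × the single-arm SE, that is 1.22 times as large. For 15/10 it is 1.76. A common drift cancels, so the expected contrast is zero at any D and the rejection rate is α. Simulation at 15/15 gave 5.06%, 5.09% and 5.05% for drifts of 0, 3 and 5.

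**The case against.** The other side has several good points.

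- **Status and wording.** H2.5 is labelled exploratory, is worded with may and might, and ends with a plan to explore and graph the trajectories. Section 2.13 says what would support the primary hypothesis and H2.1, but sets no such rule for H2.5. A reader might infer that any drift will be declared learning. The text does not say so, and only an upward drift large enough to be significant could be mistaken for it. This stands.
- **Definition of learning.** H2.5 describes a rise within participants, and the words about comparison groups attach to the acute gains, which do get a between-group test. A per-group slope does estimate that rise. But the same hypothesis interprets the rise as carry-over or skill and expects it to be largest in Groups 1 and 2, and that is a statement about differences between arms.
- **Use of the comparators.** A reader might infer that Groups 3 and 4 are left out. The trend is examined for each group, so at least Group 3's slope would appear beside the others, and nothing rules out a contrast. An unseen analysis plan may contain one. Still, the article itself names the criterion and attaches the label to it, and slopes shown side by side are not a comparison.
- **Sources of drift.** Seasonal and life changes have no fixed sign. Regression toward the mean need not favour calm in a sample limited to GAD-7 scores of 1 to 7. The protocol gives no evidence of a positive drift. This stands: drift is a possibility, not a forecast.
- **Numbers.** They rest on assumed SDs and show that a test of zero slope has power when the slope is not zero. That is correct, and it is also the point: the test responds to the slope whatever its cause.
- **Group 4.** Section 2.7 ties VAS ratings to sessions and leaves unclear whether this arm rates at all. Adding about 21 self-ratings would alter a comparator of the primary analysis. This stands and limits the remedy.

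**Conclusion.** The point holds, at low weight. Section 2.13 labels as a learning effect a within-arm trend that cannot be told apart from a drift shared by all arms, and it states no slope comparison to match the expectation about Groups 1 and 2. With 105 per arm and a common drift of 3 VAS points, one arm would show a significant upward trend in roughly 30% to 87% of trials over the main range of assumed SDs, against about 5% for the between-arm contrast. The percentages depend on assumptions that the protocol cannot confirm. That the contrast cancels a common drift while the per-group test does not holds whatever SDs are assumed.

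A reader might go further and conclude that the trial's efficacy or conditioning results are compromised. They are not: the primary ANCOVA compares randomised groups, H2.1 compares matched with mismatched scent groups, and H2.2 compares the arms at T1. What is at risk is the interpretation of one hedged exploratory finding.

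**What to change.** In 2.13, specify for the pre-session VAS mixed model a group × session-number interaction, with a random intercept and a random slope for each participant. Base any statement about learning due to the combined intervention on the slope contrast of Groups 1 and 2 versus Group 3. Add the contrast with Group 4 only if that arm already gives repeated VAS ratings; do not introduce ratings there for this purpose. Report the per-group slopes and graphs as description, without the learning-effect label.

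The cost is one sentence and one interaction term in a model already planned, with no new data. The drawback is precision: the contrast's standard error is about 1.22 times that of a single-arm slope (for example 1.76 against 1.44 points at SDs 15/10), and the quantity tested is a difference between slopes, so fewer results will be significant.

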### Qualitative analysis

2.14

A pragmatic qualitative content analysis with a combined deductive-inductive approach (29) is conducted using the software MAXQDA 2026 and oriented to the procedure outlined by Rädiger and Kuckartz (30): Responses to the open-ended questionnaire items are imported into the software and initially reviewed to gain an overview of the material and to familiarize the researchers with the data. Deductive categories are developed based on the predefined themes of the open-ended questions, while allowing for the inductive emergence of additional themes from the data. The coding framework is iteratively refined during the analysis and discussed within the research team to enhance intersubjective comprehensibility as a key quality criterion of qualitative research (31). The aim of the qualitative analysis is to synthesize the core themes emerging from participants’ experiences with the intervention.

## Discussion

3

This study is a comprehensive trial examining a novel multimodal intervention that integrates digital self-hypnosis with essential oil aromatherapy for individuals suffering from persistent worries and stress at a subclinical level. By leveraging the anxiolytic properties of lavender and bergamot essential oils in tandem with the deep relaxation of hypnosis, the study aims to enhance stress reduction outcomes and potentially condition a natural relaxation trigger, the essential oil, that participants can use beyond the intervention. The significance of this research lies in its preventive focus, because helping those with mild anxiety manage their symptoms effectively and possibly avert progression to a clinical disorder (1). If successful, the intervention could be a low-cost, easy to use tool, the essential oils are inexpensive, and the hypnosis can be delivered via an app or website, empowering individuals to self-regulate anxiety and stress in their daily lives.

Furthermore, the study will contribute to the scientific understanding of mind-body interactions, confirming whether the addition of a sensory cue can reinforce hypnotic relaxation and create lasting conditioned effects. Previous evidence shows that pleasant odors can directly influence mood and physiology (3–5, 32) and pairing them with therapy techniques may harness the brain's associative learning to prolong benefits. The outcome of this study will inform not only clinical practice in terms of combining aromatherapy with psychological interventions, but also theoretical models of how contextual cues such as essential oil can become safety signals or relaxation triggers through conditioning. A positive finding would open avenues for personalized aromatherapy in mental health, such as patients could choose an essential oil, they find comforting to integrate into their therapy, thus creating a portable cue for calm that they carry into real-world situations. The anticipated conditioning effects of lavender and bergamot essential oils are assumed to arise from their olfactory properties and the associated scent stimulus that elicit the conditioned response. Potential stress-reducing and anxiolytic pharmacological effects of the oils' bioactive constituents are not accounted for and may, however, have contributed to the observed effects that are attributed to conditioning.

An additional objective index of stress physiology would be salivary cortisol (e.g., diurnal profiles or the cortisol awakening response) (33). While such endocrine assessments were beyond the scope of the present trial, future trials building on this foundation will integrate multimodal biomarkers to more comprehensively characterize psychophysiological mechanisms and intervention effects.

In summary, this study addresses an important gap for those with subthreshold anxiety, testing an innovative approach to bolster their coping resources. By rigorously evaluating subjective, psychometric, and objective physiological outcomes, this study will clarify the efficacy of combining essential oil inhalation and self-hypnosis and examine the durability of its effects via conditioned associations. As anxiety and stress continue to be widespread issues, especially in modern fast-paced life, accessible interventions that promote relaxation and resilience are in high demand (34). This trial's findings will shed light on whether an “essential oil-conditioned hypnosis” approach can be one such effective strategy to help individuals cultivate lasting calm and improve their overall well-being. The integration of quantitative results with qualitative insights will also reveal how participants experience the intervention in daily life, guiding future refinements. Ultimately, if the hypotheses are confirmed, the combination of guided self-hypnosis and essential oils could become a practical, evidence-based method for distress reduction and mental health promotion in subclinical populations, with potential to be scaled broadly through digital health platforms.

## Ethics and dissemination

4

The study has been approved by the responsible ethics committee, and all participants provide informed consent prior to participation. The intervention is designed as a low-intensity, non-invasive digital self-help program targeting individuals with subsyndromal anxiety and stress. Guided self-hypnosis exercises are delivered in a standardized, supportive format and do not involve exposure to traumatic material or symptom provocation. Participants are informed that the intervention is not intended to replace clinical treatment and are advised to seek professional help if symptoms worsen or if clinically relevant anxiety emerges during the study. Clear information on withdrawal rights and contact options for study staff is provided throughout participation.

Potential risks associated with self-hypnosis and essential oil inhalation are considered minimal. Participants are screened for contraindications to hypnosis and essential oil use, and safety instructions regarding essential oil inhalation are provided. Adverse events will be monitored and documented throughout the study period. For the optional physiological assessments conducted in Berlin, standard safety procedures for ECG and pulse recordings are followed.

To ensure participant safety, individuals whose screening results fall close to or exceed predefined cut-off values for generalized anxiety will undergo an additional eligibility assessment prior to study inclusion. These participants will be invited to a brief virtual screening meeting with a psychologist or medical staff of the study team to clarify symptom severity, current treatment status, and potential risk factors. Study participation will only commence if it is determined that inclusion is safe and appropriate within the scope of a low-intensity, self-guided intervention. Participants for whom clinically relevant anxiety or safety concerns are identified during this secondary screening will not be enrolled and will be advised to seek appropriate professional support.

Study results will be disseminated through peer-reviewed scientific publications and conference presentations, regardless of outcome. The trial will be reported in accordance with CONSORT guidelines for randomized trials (35). In addition, aggregated and anonymized findings may be shared with participants and the broader public through accessible summaries. This dissemination strategy aims to promote transparency and support the responsible development of scalable digital interventions for stress and anxiety prevention.

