### Participants

2.2

The target population is adults (18–65 years) in Germany with subsyndromal generalized anxiety. Key inclusion criteria are: (a) GAD-7 anxiety questionnaire score between 1 and 7, indicating minimal to mild anxiety, not meeting GAD diagnostic threshold, (b) no acute psychiatric condition requiring treatment, and (c) willingness and ability to follow the 8-week intervention schedule online. Participants must reside in Germany, have sufficient German language skills, since all materials are in German, and provide informed consent online. To ensure safety, individuals are excluded if they screen positive for any serious mental health issues, such as moderate-to-severe anxiety or depression [e.g., GAD-7 ≥15, Patient Health Questionnaire (PHQ)-9 ≥20, or PHQ-9 suicidal ideation item > 1, which suggest clinical severity] (12, 13), current psychotherapy or psychiatric treatment, or a history of conditions like psychosis, bipolar disorder, post-traumatic stress disorder, or severe personality disorder. Participants with known scent sensitivities or olfactory impairments are also excluded specifically for anyone with an intolerance or aversive reaction to lavender or bergamot essential oil, or diagnosed anosmia (loss of smell), cannot take part. This screening is implemented via an initial online questionnaire (including GAD-7 and PHQ-9) before randomization. Only those who pass the screening thresholds and report no disqualifying conditions are granted access to the study portal. This procedure ensures the sample truly comprises people with subclinical anxiety levels and avoids enrolling anyone in need of more intensive treatment. If a prospective participant's responses indicate high symptom severity or risk, the system automatically excludes them and provides standardized feedback recommending appropriate help such as contacting a physician or therapist, thereby prioritizing safety.

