### Safety procedures and participant contact

2.4

The intervention is fully self-administered via the online platform; no therapeutic interaction is provided. Participants can contact the study team at any time for study-related questions. Eligibility is determined through a rule-based online screening (GAD-7, PHQ-9, treatment status, and safety-relevant history). Individuals exceeding predefined safety thresholds (e.g., GAD-7 outside the inclusion range; PHQ-9 ≥20; PHQ-9 item 9 > 1; or self-reported history of psychosis, bipolar disorder, post-traumatic stress disorder (PTSD), or severe personality disorder) are automatically excluded and receive standardized information recommending appropriate professional support and crisis resources. In rare borderline or ambiguous cases, a brief structured safety call (approx. 3–5 min) is conducted by psychology-trained study staff to confirm that participation in a low-intensity self-help intervention is appropriate. This safety call is not diagnostic or therapeutic. Enrollment proceeds only if no indications of treatment-requiring symptom severity are present.

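### Section 4 allows an interview and possible enrolment for applicants above the anxiety cut-off, whom sections 2.2 and 2.4 refuse outright

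*Protocol article*

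**What the plan says.** **Section 2.2 (Participants)** requires a "GAD-7 anxiety questionnaire score between 1 and 7". It gives GAD-7 ≥15 as an example of an excluding score and continues: "Only those who pass the screening thresholds and report no disqualifying conditions are granted access to the study portal". It then states what this achieves: "This procedure ensures the sample truly comprises people with subclinical anxiety levels".

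**Section 2.4 (Safety procedures and participant contact)** describes a rule-based online screen. It begins "Individuals exceeding predefined safety thresholds (e.g., GAD-7 outside the inclusion range", lists further triggers, and says that these people "are automatically excluded and receive standardized information recommending appropriate professional support and crisis resources". It also provides a personal check: "In rare borderline or ambiguous cases, a brief structured safety call (approx. 3–5 min) is conducted by psychology-trained study staff". Enrolment after that call requires that nothing points to severity needing treatment.

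**Section 4 (Ethics and dissemination)** says "individuals whose screening results fall close to or exceed predefined cut-off values for generalized anxiety will undergo an additional eligibility assessment". The assessment is a short virtual meeting with a psychologist or medical staff. Then: "Study participation will only commence if it is determined that inclusion is safe and appropriate within the scope of a low-intensity, self-guided intervention". Anyone found to have clinically relevant anxiety or a safety concern is not enrolled. No value is given for the cut-off.

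**The concern.** Under section 2 a high GAD-7 score ends the application by rule, with no human step. Under section 4 a score above the cut-off leads to a meeting that can end in enrolment. Both cannot apply to one applicant, and staff following different sections could treat the same score differently.

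Three things depend on the answer:

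- **Safety.** The programme is fully self-administered with no therapeutic interaction, so screening is one of the main safeguards.
- **The population.** The assurance in section 2.2 that the sample is subclinical rests on the 1–7 limit being firm. An override with no upper bound would remove that basis.
- **Interpretation.** GAD-7 is also a secondary outcome analysed with baseline adjustment (sections 2.9 and 2.13). Readers need to know which baseline range was admitted.

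**Working it through.** The plan gives no figure to reproduce here. The check compares the stated rules score by score.

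**Inputs**

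- Inclusion range 1–7 (section 2.2).
- Example exclusion GAD-7 ≥15 (section 2.2).
- Automatic exclusion of any GAD-7 outside the range (section 2.4).
- Meeting for scores close to or above an unnamed cut-off, with possible enrolment (section 4).
- Assumed, not in the article: GAD-7 totals run from 0 to 21, and *close to* means within 1 to 3 points.

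**Two readings of the section 4 cut-off:** 7 (top of the inclusion range) or 15 (the example exclusion value).

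| GAD-7 | Sections 2.2 and 2.4 | Section 4, cut-off 7 | Section 4, cut-off 15 |
|---|---|---|---|
| 9 | Refused | Meeting, may be enrolled | Not covered |
| 14 | Refused | Meeting, may be enrolled | Meeting (close to), may be enrolled |
| 16 | Refused | Meeting, enrolment unlikely | Meeting, enrolment unlikely |

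At 16, section 4's own bar on clinically relevant anxiety would probably stop enrolment. At 9 it might well not.

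**Score values with two dispositions**

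- Cut-off 7: scores 8 to 21, so 21 − 8 + 1 = 14 values.
- Cut-off 15, exceeding only: 15–21 gives 21 − 15 + 1 = 7 values if a score at the cut-off counts. Otherwise 16–21 gives 21 − 16 + 1 = 6.
- Cut-off 15, adding *close to*: a width of 1 point adds 14, 2 points adds 13–14, and 3 points adds 12–14. A score of 15 is covered either way, so the totals are 8 (14–21), 9 (13–21) or 10 (12–21). All lie outside 1–7.

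These counts show how far the overlap reaches on the scale. They do not measure how many applicants fall in it, which the article does not give.

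**The personal check itself.** Section 2.4 has a 3–5 minute call by psychology-trained staff, declared neither diagnostic nor therapeutic, for rare unclear cases. Section 4 has a virtual meeting with a psychologist or medical staff to clarify severity, treatment status and risk. Both end in a similar bar, so this second difference is minor.

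**The case against.** The strongest defence is that section 4 never says the inclusion criteria are waived. Its condition on starting participation is a necessary one, so the meeting could be a further gate for people who must still score 1–7. On this view section 4 merely elaborates the borderline call in section 2.4, and both bar clinically relevant severity. That reading works for scores *close to* a cut-off of 7. It does not work for scores that exceed the cut-off: section 2.4 has already excluded those people, and a meeting on their eligibility would have no purpose.

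Other points stand in part:

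- Section 2.2 ties automatic exclusion by the system to high severity or risk. Scores of 8–14 fail there only through the inclusion criterion and the portal-access rule; section 2.4 makes their exclusion automatic. The outcome is the same.
- Read with section 2.4, the natural referent of the section 4 cut-off is the inclusion range, which makes the reading of 15 less likely. That leaves the reading of 7, under which the conflict is widest.
- An article need not repeat every number or the full procedure for the call. Here, however, the problem is two stated rules that disagree, not a missing detail.

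**Conclusion.** The concern holds: the eligibility rule is wrong as written. On either reading of the cut-off, some scores are both excluded automatically and sent to a meeting that may admit them: 14 values if the cut-off is 7, and 8 to 10 if it is 15 with *close to* counted. These counts rest on an assumed 0–21 scale and, for the second, an assumed width of 1 to 3 points. The conflict itself rests on neither assumption.

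The consequence is limited. Screening comes before randomisation, so the between-arm comparison is not biased, and the primary endpoint, analysis model and sample size are untouched. Section 4's closing bar would probably keep out the most severe cases. What remains is an eligibility limit that is a fixed rule in one section and a staff judgement in another. It should be fixed.

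**What to change.** In section 4, state that a GAD-7 score outside 1–7 is excluded with no override. Delete the words *or exceed* and name the cut-off as 7; deleting the words alone would leave the conflict if 15 were meant. Limit the personal check to a named band inside the range (for the investigators to choose, for example 6–7) or to ambiguous answers. Use one description of that check, covering format, staff and decision, in sections 2.4 and 4. Confirm that the SoSci screening logic applies the same rule.

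If the investigators and the ethics committee do intend an override, write it as an eligibility criterion with an upper GAD-7 limit, carry it into sections 2.2 and 2.4, and record which participants entered through it.

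The cost is wording in two sections and a check of the software. An ethics notification is needed only if an override is intended or the approved text differs.
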